## Methods/design

### Study design

This is a before-and after study to evaluate the impact and feasibility of upscaling CC screening and treatment services for WLWH attending a rural referral CTC in Tanzania. The main objective is to evaluate the uptake by WLWH attending screening after implementation of HPV testing on a self-sampled cervico-vaginal smear, compared to a retrospective cohort screened by VIA. HPV testing has been implemented in a bundle with: a) a smartphone integrating a mobile colposcope (EVA system, Mobile ODT, Israel) for digital enhancement of VIA examination with cervix magnification and second look/quality control; b) thermal ablation in place of cryotherapy (thus avoiding the need for replenishing nitrogen gas cartridges); and c) LEEP.

We adopted an uncontrolled before-and-after design to compare proportion of WLWH attending screening before and after implementing mentioned interventions. A sub-study with cross-sectional design aims to explore diagnostic performance of two novel tests: the first, QuantiGene-Molecular-Profiling-Histology (QG-MPH), is based on transcriptomic biomarker analysis, while the second is a serological assay to detect antibodies against HPV16-L1 [29], either with a qualitative (Prevo-Check®) or quantitative (PT Monitor®) approach (Table 1. Supplementary material Annex A1 and A2). Further objectives are to determine the adherence to recommendations after screening, to assess the prevalence of HPV genotype-specific infection as well as other co-infections, and to assess feasibility, acceptability and costs of the new implemented screening and treatment plan.

**Table 1 Tab1:** Novel assays

Test	Name	Target	Description
Lateral Flow Assay (LFA)	PT Monitor® (Abviris GmbH, Germany)	HPV16-L1 Ab	Blood-based (serum) competitive immunoassay assessing the presence of epitope-specific antibodies against HPV16-L1. Elevated levels of these antibodies are associated with the presence of HPV16-induced cancer or pre-cancer. A quantitative readout is possible with an optical table-top reader (aLF reader by Qiagen, Germany). CE-marked IVD
Rapid Lateral Flow Assay (rLFA)	Prevo-Check® (Abviris GmbH, Germany)	HPV16-L1 Ab	Qualitative (yes/no) output of LFA (PT Monitor®) in form of rapid capillary point-of-care test with a cut-off of HPV16-L1 Ab > 1000 ng/ml. CE-IVD-marked for the detection of HPV16-induced anal and oropharyngeal cancers

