### Endpoints

The primary endpoint is screening coverage, defined as the proportion of WLWH enrolled in KIULARCO screened for CC in the 12 months period after implementation of HPV testing. Participants that undergo screening and transfer out to other CTC within the study period are also included. Secondary endpoints are listed in Table 3.

**Table 3 Tab3:** Endpoints

	Endpoint
**HPV prevalence & persistence**	Proportion of participants with documented HR-HPV, LR-HPV and HPV negative at baseline
	HPV genotypes at baseline
	Proportion of participants with documented HR-HPV, LR-HPV and HPV negative at follow up (6 months after the first sample)
	HPV genotypes at follow up (6 months after the first sample)
	Rate of clearance and persistence of HPV at 6 months follow-up and factors associated with viral persistence
**Cervical lesions**	Prevalence of cervical dysplasia among the patients with HR-HPV
	Prevalence of co-infection (STI and GS)
**QG-MPH® performance**	Prevalence of HSIL/CC detected by QG-MPH® in cervical smear samples
	Diagnostic test accuracy (sensitivity, specificity, PPV, NPV) in detecting patients with CIN3 + compared to colposcopy images, HPV infection detected by Seegene Anyplex ™ II 28 and histology
**Prevo-check® performance**	Prevalence of HPV16 positive CIN2 + detected by Prevo-check®
	Diagnostic test accuracy (sensitivity, specificity, PPV, NPV) in detecting patients with HPV 16 compared to Seegene Anyplex ™ II 28
**PT Monitor® performance**	Comparison of HPV16-antibody levels in women with and without HPV16-positive CIN2 + . Calculation of test performance parameters (sensitivity, specificity, PPV, NPV) at different antibody thresholds and calculation of optimum cut-off for CIN2 + detection by ROC analysis and Youden index
	Diagnostic test accuracies (sensitivity, specificity, PPV, NPV) in detecting patients with HPV16-induced CIN2 + by PT Monitor® compared to colposcopy images, HPV infection detected by Seegene Anyplex ™ II HPV 28 Detection and histology
**Screening strategy implementation**	Acceptability of cervical self-sampling
	Acceptability of proposed implemented pathway
	Adherence to follow-up
	Rate of WLWH completing the CC screening and treatment care plan
	Prevalence of cryo/thermoablation-non-eligible lesions treated with LEEP

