### Statistical analysis

For the primary endpoint, the hypothesis is that implementing a bundle of interventions comprising HPV testing on self-collected samples will improve rates of CC screening among WLWH enrolled in KIULARCO from 8 to 30%. Due to the uncertainty about the WLWH population size, this hypothesis is considered as exploratory, therefore only the precision of the proportion is estimated (screening rate), with a 95% confidence interval. The proportion of WLWH attending CC screening in the post-period will be estimated with 95% confidence interval.

For the secondary and other endpoints no hypothesis will be formulated and results will be compared in an exploratory manner. Diagnostic test accuracies (sensitivity, specificity, positive predictive value and negative predictive value) will be calculated for comparison. Accuracies will be calculated with a 95% confidence interval. Prevalence of secondary endpoints will also be estimated with 95% CI's. Diagnostic tests will be pairwise compared using McNemar test. The assessment of acceptability and feasibility will be evaluated with exploratory statistics. The agreement of raters between diagnostic interpretations will be described with kappa coefficients and polychoric correlations. All secondary parameters will be reported with descriptive statistics including minimum and maximum values, interquartile range, median, mean, SD, count, and proportion as appropriate. Comparisons between study groups will be done using Kruskall-Wallis test for metric or ordinal data and Fisher's exact test for categorical data. A *p*-value < 0.05 (two-sided) is considered as statistically significant.

All evaluations will be done with the latest version of the statistical software R.

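### Table 3 gives each novel test a different accuracy target, while the analysis section plans pairwise McNemar tests with no shared target; Prevo-Check has no lesion-based accuracy, and PT Monitor's Youden cut-off has no named optimism correction

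*Protocol article*

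**What the plan says.** In the Statistical analysis section of the protocol article, the four accuracy measures are computed so that tests can be compared: "Diagnostic test accuracies (sensitivity, specificity, positive predictive value and negative predictive value) will be calculated for comparison". The next step is "Diagnostic tests will be pairwise compared using McNemar test". No pairs, target condition or subgroup are named. The same section states "For the secondary and other endpoints no hypothesis will be formulated and results will be compared in an exploratory manner", yet keeps a threshold of p < 0.05 ("two-sided) is considered as statistically significant").

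Table 3 (Endpoints) sets these accuracy targets:

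- **QG-MPH:** "Diagnostic test accuracy (sensitivity, specificity, PPV, NPV) in detecting patients with CIN3 + compared to colposcopy images", together with the Anyplex HPV result and histology.
- **Prevo-Check:** "Diagnostic test accuracy (sensitivity, specificity, PPV, NPV) in detecting patients with HPV 16 compared to Seegene Anyplex". Its other endpoint is the prevalence of HPV16-positive CIN2+ that it detects.
- **PT Monitor:** HPV16-induced CIN2+ against colposcopy images, the Anyplex HPV result and histology. Performance is also planned at several antibody thresholds, and an optimum cut-off is sought for CIN2+ "detection by ROC analysis and Youden index".

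Table 1 describes Prevo-Check as the yes/no form of PT Monitor with a cut-off above 1000 ng/ml. It says of the antibody: "Elevated levels of these antibodies are associated with the presence of HPV16-induced cancer or pre-cancer".

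**The concern.** A paired test of accuracy asks whether two tests differ in how often they are right about the same condition in the same women. No two of the three novel tests share an accuracy target in Table 3. If each is scored on its own target, a small p-value may show only that the targets differ.

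The Background presents the novel tests as a way to find women who need treatment where HPV testing is too unspecific. For that purpose the lesion is the relevant target. Prevo-Check and PT Monitor read the same antibody, but one is scored on infection and the other on lesions. Prevo-Check could look weak for missing infections without a lesion.

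A cut-off that maximises the Youden index in a data set also looks better in that data set than it would in new women. At stake is what the sub-study can say about which test, at which threshold, deserves further work as a triage tool.

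**Working it through.** **The plan's own figure.** The article's only precision figure concerns the screening proportion with 1200 women: 1.96 × √(0.30 × 0.70 / 1200) = 2.6 points and 1.96 × √(0.10 × 0.90 / 1200) = 1.7 points. Both lie within the stated ±3% and ±2%. It does not bear on this point, and no figure is given for the diagnostic sub-study. The inputs below are therefore assumptions, except N = 1200 (Sample size) and 150 controls (the HR-HPV-negative control group in Physical examination / mobile colposcopy).

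**Step 1: one test scored on two targets.** Assume 1200 women, HPV16 prevalence 5% or 10%, and 10% to 50% of HPV16-positive women with CIN2+. Assume an antibody test positive in 80% of women with HPV16-positive CIN2+, 20% of HPV16-positive women without a lesion, and 5% of HPV16-negative women.

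Sensitivity for the lesion is 0.80 by assumption. Sensitivity for infection is (0.80 × D + 0.20 × I) / (D + I), where D is the number of HPV16-positive women with CIN2+ and I the number without.

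- Prevalence 5%, 10% with lesions: D = 6, I = 54, so (4.8 + 10.8) / 60 = 0.26.
- Prevalence 5%, 50% with lesions: D = 30, I = 30, so (24 + 6) / 60 = 0.50.

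The same readings thus give 0.80 for lesions and 0.26 to 0.50 for infection.

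**Step 2: McNemar on those readings.** Compare correct with incorrect on the two targets. Only infected women without a lesion are discordant: 0.20 × I are right on infection only, and 0.80 × I are right on the lesion only.

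| HPV16 prevalence | With CIN2+ | Discordant | Exact p |
|---|---|---|---|
| 5% | 10% | 11 vs 43 | 1.4 × 10⁻⁵ |
| 5% | 50% | 6 vs 24 | 0.0014 |
| 10% | 10% | 22 vs 86 | 4 × 10⁻¹⁰ |
| 10% | 50% | 12 vs 48 | 3.2 × 10⁻⁶ |

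A test differs significantly from itself because the target changed. This is an illustration, not an analysis the article announces.

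**Step 3: optimism at the Youden cut-off.** Youden index J = sensitivity + specificity − 1. In each simulated data set (normal marker in cases and controls, 2000 replicates) the cut-off maximising J was chosen. The table shows mean apparent J minus true J at that cut-off.

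| Controls | AUC | 15 cases | 30 cases | 60 cases |
|---|---|---|---|---|
| 500 | 0.65 | 0.14 | 0.10 | 0.07 |
| 500 | 0.75 | 0.12 | 0.08 | 0.06 |
| 500 | 0.85 | 0.11 | 0.07 | 0.05 |
| 150 | 0.65 | 0.14 | 0.10 | 0.07 |
| 150 | 0.75 | 0.13 | 0.09 | 0.07 |
| 150 | 0.85 | 0.11 | 0.08 | 0.05 |

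Over a wider grid (1200 women in all, 10 to 80 cases, AUC 0.5 to 0.9, 800 replicates) the excess runs from 0.04 to 0.18. Nearly all of it falls on sensitivity: at AUC 0.7 with 20 cases, apparent sensitivity is 0.72 and true sensitivity 0.61, while specificity is 0.66 either way.

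**The case against.** The strongest defence is that the article does not commit the error. It names no McNemar pairs and does not say that the Table 3 endpoints are the quantities compared. All tests are planned in the same participants, and QG-MPH and PT Monitor share a list of comparators, so a valid same-target comparison is possible. Such detail often sits in an analysis plan that is not shown. This stands in part: a reader might infer that cross-target tests are declared, and the text does not support that. What remains is that the article fixes different targets and an unqualified comparison rule, and the two do not fit together.

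A reader might also infer that McNemar is planned for PPV and NPV. The sentence does not say so. Those measures are only listed as calculated for comparison, so the point matters only if they are tested.

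On Prevo-Check, agreement with HPV16 PCR is a reasonable descriptive measure, since PCR is planned for every participant. Lesion accuracy of the antibody is also covered through PT Monitor. That stands, but it gives no lesion accuracy for the yes/no point-of-care format, whose CIN2+ endpoint is only a prevalence.

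It is tempting to say that PT Monitor ignores its own pre-set threshold. Table 1 gives 1000 ng/ml in the Prevo-Check row only. Table 3 also plans PT Monitor results at several thresholds, and does not say that its separate accuracy endpoint uses the Youden cut-off. That derivation and evaluation use the same women is inferred from the absence of a second sample; internal validation may be described elsewhere. Seeking a candidate cut-off is a normal exploratory aim.

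**Conclusion.** The concern holds in a limited form, as a worthwhile improvement to exploratory secondary analyses.

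- **McNemar.** Table 3 sets three targets for three tests and the comparison rule names none. Applied to those endpoints, the p-values would not measure accuracy differences. The exploratory label lowers the stakes but does not make such a comparison valid.
- **Prevo-Check.** This is a mismatch between target and stated purpose, not optimism. Under the assumed positivity rates, sensitivity of 0.80 for lesions would appear as 0.26 to 0.50 for infection, so the test would be understated.
- **PT Monitor.** Only the result at the Youden cut-off is optimistic, by about 0.05 to 0.15 in J for 15 to 60 cases, if no correction is applied.

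A reader might conclude that the whole accuracy programme is invalid or inflated. The article does not support that: the directions differ, the several-threshold results are not tuned, and each accuracy estimate still answers its own question. All sizes rest on assumed case numbers, control numbers, AUC and positivity rates. The primary endpoint is not touched.

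**What to change.** 1. Add Prevo-Check accuracy for HPV16-positive CIN2+, and for CIN2+, on the same reference as PT Monitor. Keep agreement with HPV16 PCR as a descriptive result.
2. Restrict McNemar to pairs of tests scored on the same target and reference, run separately in diseased women (sensitivity) and non-diseased women (specificity). If PPV or NPV are compared, use a generalised score or bootstrap method, because their denominators differ between tests.
3. Label the Youden result for PT Monitor as cut-off derivation and report it with a bootstrap optimism correction that repeats the cut-off search in each resample. Performance at 1000 ng/ml can be shown alongside as a pre-set threshold, noting that it is stated for Prevo-Check; it need not become the main PT Monitor result.

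The cost is analysis wording and code. The measurements are already planned, so no further data collection is needed. The downside is slightly less favourable PT Monitor figures.

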#### Physical examination / mobile colposcopy

The first participants will undergo physical examination and VIA at baseline visit, in accordance with the national guidelines, as well as HPV-testing as detailed further, until 150 HR-HPV negatives have been examined as a control population for the diagnostic sub-study. Thereafter, only participants that report vaginal symptoms (e.g., vaginal discomfort, abnormal vaginal discharge, pelvic pain, abnormal vaginal bleeding, suspected STI or CC) and/or test positive at rLFA will undergo physical examination at baseline. Otherwise, physical examination is reserved for participants with detected HR-HPV infection, and this will take place at a second visit, due to laboratory turnaround time. Physical examination is performed as per local routine, i.e., with speculum and VIA, in accordance to WHO/IARC standard recommendations [33]. Images are recorded with the aid of a mobile colposcope (EVA system®, MobileODT Ltd, Tel Aviv-Yafo, Israel). Lesion interpretation and classification will be done as specified in Annex A. If the lesion is compatible with an STI or GS, recommendations for treatment will be provided according to National Guidelines [17]. Precancerous lesions will be treated according to severity (Fig. 1 Study Algorithm; Supplementary materials: Annex B).

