	Service accessibility (means of travel to the point of screening: foot, car bajaj, public transport bus; distance to hospital < 5 km, 5—10 km, > 10 km, perceived difficulty of travel yes/no; mean of waiting time in minutes at point of screening)
	Social and educational status of WLWH attending and refusing CC screening as well as their awareness regarding HPV infection, transmission, risk behavior, CC
**Costs**	Direct and indirect costs associated with CC screening and treatment before and after the proposed implementation was adopted including the bundle of interventions
	Direct and indirect costs, as well visit durations, for the current VIA and cryotherapy standard of care and for the implemented path with HPV-based triage

*Abbreviations**: **CC* Cervical cancer, *CIN* Cervical intraepithelial neoplasia, *GS* Female genital schistosomiasis, *HSIL* High Grade Squamous Intraepithelial Lesion, *HPV* Human Papilloma Virus, *HR* High-risk, *LFA* Lateral Flow Assay, *LR* Low risk, *NPV* Negative predictive value, *RNA* Ribonucleic acid, *QGMPH* QuantiGene-Molecular-Profiling-Histology, *STI* Sexual transmitted infection, *PPV* Positive predictive value, VIA Visual Inspection with Acetic Acid, *WLWH* Women living with HIV

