## Discussion

This implementation project represents a micro-initiative, at rural referral hospital level, to contribute to the efforts of improving CC prevention and the care cascade in Tanzania, complying with the WHO and national recommendations regarding secondary and, in part, tertiary prevention. The choice of implementing treatment procedures along with HPV testing has an ethical rationale. The decision to substitute the already in-use cryotherapy with a thermal ablation device was made after frequent reports of cryotherapy gas supply challenges, with consequently missed treatment opportunities. The introduction of a mobile digital colposcope had the purpose of allowing second-look evaluations by collaborating clinicians, for continuous education and for quality improvement. The choice of a laboratory-based HPV testing platform over the on-site available Xpert® platform was firstly due to concurrent testing needs (esp. for tuberculosis diagnostics) which would have hampered an HPV-based single-visit screen-and-treat approach only, and secondarily because the chosen platform allows for identifying more individual genotypes. The choice of a before-and-after study design has certain limitations, in that the intervention effect may be overestimated by unrecorded, concurrent factors (e.g., in this case: increased patient sensitization to CC, training of personnel, screening offered 5 days a week instead of twice weekly, and financial incentives to staff performing screening), which in this case are relevant to some extent, since the ideal comparison is the WHO’s second target (70% screened). Further, the low estimates of pre-intervention screening rates (8%) may reflect incomplete reporting or heterogeneous data sources. For the purpose of this study, a digital case report form (e-CRF) was developed which could be accessed via a tablet device or computer (also provided) and filled out in real-time. This should minimize bias in data collection. Considering that CC screening was already routinely offered to the study population and that reporting may be of suboptimal quality, recall bias cannot be ruled out for the patients who had previous diagnosis of precancerous lesions, although this should not affect the primary outcome. Cost of service is a major concern regarding the sustainability of the implementation project, which we plan to address in a future publication. Provided free of charge or after a symbolic financial contribution, CC screening and treatment with VIA / cryotherapy was financially supported by non-governmental implementing partners, including financial incentives to the screening team and an additional outreach program. Currently, diagnostic and therapeutic options are limited in peripheral health-care centers of Tanzania and different factors hinder access to CC screening and treatment programs. Implementing “near-home” options may substantially increase the participation rate as well as improve the adherence to the appropriate care plan, with rationalization of health-care center resources and improvement of quality of services.

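### Read literally, the blanket Kruskal-Wallis rule covers the cost endpoints, but a rank test does not address the difference in mean cost per woman

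*Protocol article*

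**What the plan says.** All places are in the protocol article.

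- **Statistical analysis.** The rule for group comparisons is "Comparisons between study groups will be done using Kruskall-Wallis test for metric or ordinal data", and a p-value "< 0.05 (two-sided) is considered as statistically significant". The same section sets no hypotheses for the secondary endpoints, calls their comparison exploratory, and has mean and SD reported beside median and IQR. It names neither cost nor visit duration and does not define the study groups.
- **Endpoints, Table 3 (Costs).** Two entries: "Direct and indirect costs associated with CC screening and treatment before and after the proposed implementation was adopted including the bundle of interventions" and "Direct and indirect costs, as well visit durations, for the current VIA and cryotherapy standard of care and for the implemented path with HPV-based triage". Neither names a summary measure.
- **Physical examination / mobile colposcopy.** For women with detected HR-HPV who were not examined at baseline, "this will take place at a second visit, due to laboratory turnaround time".
- **Discussion.** "Cost of service is a major concern regarding the sustainability of the implementation project"; the authors leave this topic to a later paper.

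**The concern.** Costs are metric and are compared between two periods or pathways. The only inferential method the article fixes for such data is the rank test. The decision the costs inform is whether the service can be sustained. That depends on total spending, which is the number of women multiplied by the arithmetic mean cost per woman.

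Kruskal-Wallis with two groups asks whether a randomly chosen woman in one group tends to cost more than one in the other. It answers the question about means only when the two distributions have the same shape. Here they probably do not. In the new pathway many women have a self-sampling visit and nothing more, while others add an examination visit and some add LEEP. A rank test mainly reflects the cheaper majority and gives little weight to how much the others cost. The p-value could therefore suggest a saving that the budget does not show, or miss a real increase.

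**Working it through.** **Plan's own figure.** There is none for this comparison. The Sample size section gives precision for screening coverage only.

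**Inputs from the article.** HR-HPV prevalence up to 46.7% (Background); about 2500 women under care (Setting); 8% screened before implementation (Statistical analysis); 1200 women (Sample size). Group sizes for illustration: 0.08 × 2500 = 200 before and 1200 after.

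**Assumptions not in the article.** A second visit costs the same as a VIA visit (set to 1); within-visit coefficient of variation (CV) is 20% to 50%; HR-HPV prevalence p is 25% to 46.7%; costs are lognormal. That 200 and 1200 women would have individual cost records is also assumed.

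**Step 1: why ranks and means separate.** Let the first HPV-pathway visit have mean cost f, with a second visit of mean 1 added with probability p. Mean cost per woman is f + p, so the means are equal when f = 1 − p. Take p = 0.30 and f = 0.70 and ignore variation within visits. The mean is 0.70 × 0.70 + 0.30 × 1.70 = 0.49 + 0.51 = 1.00, the same as VIA. Yet 70% of HPV-pathway women cost less than a VIA woman, whereas the rank-test null needs 50%.

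**Step 2: equal true means (f = 1 − p), share of runs with p < 0.05 for Kruskal-Wallis.**

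| p | CV 20% | CV 30% | CV 50% |
|---|---|---|---|
| 0.25 | 1.00 | 0.98 | 0.37 |
| 0.30 | 1.00 | 0.99 | 0.41 |
| 0.40 | 1.00 | 0.95 | 0.47 |
| 0.467 | 0.56 | 0.68 | 0.40 |

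Every rejection ranked the HPV pathway lower. Welch's comparison of means rejected in 3% to 7% across the original run and its repeats.

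**Step 3: HPV pathway truly 10% dearer (f = 1.1 − p).** Welch detected the increase in 68% to 100% of runs. Kruskal-Wallis rejected in 0.5% to 71%. At CV 20% its rejections pointed the wrong way (up to 71%, at p = 0.30, where f = 0.80). At CV 50% it rejected in only 7% to 15%, almost always in the right direction, so there the failure is lost power.

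**Step 4: first-visit cost fixed independently of p.**

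- f = 1.0 or 1.2: both tests call the HPV pathway dearer in more than 99% of runs.
- f = 0.9: no wrong-direction rejections, but Kruskal-Wallis power runs from 4.5% to 100%. At p = 0.25 and CV 20% the true mean is 0.9 + 0.25 = 1.15; Kruskal-Wallis detects this in about 5% of runs and Welch in 100%.
- f = 0.6 to 0.8: wrong-direction rejections appear.

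**Step 5: a different cost model.** Lognormal costs with equal means, log-SD the same or different in the two groups.

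| Log-SD, before / after | n 200/1200 | n 200/200 | n 100/300 |
|---|---|---|---|
| 0.5 / 0.5 | 5.0% | 5.5% | 4.7% |
| 0.5 / 0.7 | 74% | 47% | 39% |
| 0.8 / 1.0 | 73% | 49% | 36% |
| 0.5 / 1.0 | 100% | 99.7% | 99% |

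Welch rejected in 4% to 7% throughout. With the new mean 15% higher (0.5 / 1.0, n 200/1200), Kruskal-Wallis ranked it significantly lower in 99% of runs. The ratio of medians there is 1.15 × exp(−(1.0² − 0.5²)/2) = 1.15 × exp(−0.375) = 0.79. As in Step 4, reversal occurs when the typical woman is clearly cheaper on the new pathway.

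**The case against.** A reader might infer that the plan will use Kruskal-Wallis to declare the HPV pathway significantly cheaper or shorter. The article does not support that.

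- The test reaches costs only through a general sentence. Secondary comparisons are exploratory and carry no hypothesis, means and SDs would stand beside any p-value, and costing is left to a later paper. This stands and limits the weight of the point. It does not remove it: Table 3 keeps cost as an endpoint, and no other inferential method is given for metric comparisons.
- For visit duration a rank test is a legitimate choice. Table 3 refers to visits, not to total time per woman. Waiting time is listed under accessibility as a mean, with no group comparison stated. This stands, so the point is about cost.
- The two-part shape is diluted. The first participants are all examined at baseline until 150 HR-HPV negatives have been seen, and symptomatic or rLFA-positive women are examined at baseline after that. The VIA side has its own expensive tail of biopsy, hysterectomy and referral (Setting). This stands: different shapes are likely but not guaranteed.
- A reader might also infer that the conclusion would come out in the wrong direction. That needs a first visit well below the cost of a VIA visit. Nothing in the article supports such a price, and the first visit includes a brush, a rapid test, serology and 28-type PCR. This stands.
- The comparator is retrospective, with attendance and results on cards and paper registers (Study design; Data collection and management). Individual costs for the earlier period may not exist. This stands, and it limits the remedy as much as the criticism.

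**Conclusion.** The concern holds in limited form. As worded, the rule covers the cost endpoints without naming them, and it does not estimate or test the difference in mean cost per woman on which sustainability depends. The p-value can be significant at equal means (about 36% to 100% of runs across the two models when shapes differ, against about 5% when they match), or it can miss a real increase (about 5% power against 100% for Welch in one cell). Size and direction depend on assumed visit costs, variability and group sizes. If the first visit costs as much as a VIA visit or more, the two tests agree in the two-part model. It is a minor point on an exploratory secondary endpoint.

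**What to change.** Add one sentence to Statistical analysis, for example: *Costs per woman (and total staff or visit time per woman, if used as a resource measure) are exempt from the Kruskal-Wallis rule; where per-woman data exist for both periods, they will be compared as the difference in arithmetic means with a bootstrap or Welch 95% confidence interval, with median and IQR as description.* Keep Kruskal-Wallis for ordinal data, antibody levels and, if wanted, single-visit durations.

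The cost is one sentence and a few lines of R. The interval for the mean will be more sensitive to a few expensive cases, such as LEEP or referral. If the earlier period has no per-woman cost records, neither the rank test nor this interval can be computed, and the plan should then say that costs will be reported descriptively.
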